The primary outcome measure is paracentesis free survival. With an estimated probability of paracentesis free survival set to 0.3 at the end of the trial, an allocation ratio of 1:1, alpha 5% and power 80%, the required sample size is estimated to be a total of 28 patients (14 patients in each group). After taking into account the risk of participant dropout the sample size is set to be 32 patients (16 patients in each group).

Statistical analyses

We plan to include all patients randomised (intention to treat) regardless of compliance or follow up. Patient characteristics will be summarised using medians with interquartile range or proportions. Groups will be compared using t-tests or chi-square tests as appropriate. The level of significance will be set to 5%. The primary outcome measure will be evaluated using Kaplan Meier Plots and log-rank tests. Univariate and multivariate logistic regression analysis will be conducted to identify potential predictors of paracentesis free survival.

Handling of data

Data will be retrieved from medical records, information provided by the patients at trial visits as well as laboratory (biochemistry) assessments and investigational results. Data will be collected to Case report forms and entered into an electronic database by the principal investigator. Case report forms from the supporting sites will be sent by secure mail to the principal investigator. The database is anonymous. A trial participant identification list will be stored safely by the principal investigator.

Missing data

During the trial, we plan to search for information about missing data in the medical records. Investigators will pursue the options of repeating biochemistry and blood analyses when this is possible. Invasive procedures will not be repeated, should data be missing after the participant has completed the trial investigations.

Quality Control

The study personnel will be trained and tested in all study related procedures to ensure adequate quality control. In particular, investigators will be tested 0to ensure the optimal use of the interventions assessed (PleurX and large volume paracentesis). All investigators are specialised hepatologists with extensive experience in the management and observation of patients with refractory ascites including experience in the use of the PleurX and large volume paracentesis through their clinical work.

Data registration and rules for the control of investigation procedures

The study will be conducted in accordance with the applicable rules regarding quality control and quality management in clinical trials involving people and will follow EN ISO 14155- ”Clinical investigation of medical devices for human subjects – Good clinical practice.

The investigator and co-investigators at the clinical sites are responsible for managing and archiving data in accordance with current regulations. The data belongs to the investigator and co-investigators at the Gastro Unit at Hvidovre Copenhagen University Hospital.

Case Report Forms

A Case Report Form (CRF) will be completed for each patient included in the study. This will be signed by the investigator to confirm the accuracy of the data. Corrections to the data will only be made by crossing out the incorrect data (the incorrect information will remain visible and legible) with the correct data written next to the deleted data. Correction fluid will not be used. Corrections will be dated and signed by the investigator or their deputy.

Monitoring

Copenhagen University Hospital GCP unit

[name]

[name]

[name]

[contact]

Training

The investigator will ensure that the personnel involved are appropriately trained and qualified, and have the necessary information to carry out the study.

PATIENT SAFETY AND ETHICS

Informed Consent Process

The informed consent process will include both written and oral information using the prespecified forms. We will review and discuss risks and possible benefits of study participation with participants and their families. An approved consent form describing in detail the study procedures and risks will be given to the participant. The participant is required to read and review the document or have the document read to him or her. The investigator or designee will explain the research study to the participant and answer any questions that may arise. The participant will sign the informed consent document prior to any study-related assessments or procedures. Participants will be given the opportunity to discuss the study with their family or think about it prior to agreeing to participate. They may withdraw consent at any time throughout the course of the study. A copy of the signed informed consent document will be given to participants for their own records.

Participant Confidentiality

The participants will sign a consent form that allows investigators access to hospital records. Participant confidentiality is extended to cover any study information relating to participants. The study protocol, documentation, data, and all other information generated will be held in strict confidence. No information concerning the study or the data will be released to any unauthorized third party. Study investigators and scientific medical advisers will have access to study data. When conveying study materiel to external data assessors the materiel will be anonymized.

Study Records Retention

Study records will be maintained for at least five years from the date that the study is completed.

Respect for the patients physical and mental integrity and privacy

This study will be conducted according to the Danish national legislation on health. The study will be reported to the Regional Science Ethics Committee of the capital region of Denmark. The permission from The Regional Data Protection Agency will be sought and is awaited before the initiation of the study. Authorities will have full access to data, documents and registration procedures during monitoring, audits and inspections. Both oral and written informed consent will be obtained before entering the study according to the Declaration of Helsinki V and the Regional Science Ethics Committee of the capital region of Denmark. The study will comply with the law on personal data.

Ethical considerations

The PleurX catheter has proven efficient in the handling of malignant ascites by relieving symptoms and improving quality of life in this patient group. Our main aim is to give patients with ascites due to cirrhosis the same options in handling an invalidating complication to their disease, and achieve higher impact and involvement in the disease course. We also aim to diminish number of days spent in hospital and thereby adding to quality of life and well-being of the patient. The discomfort applied on the patient at the PleurX catheter placement exceeds that of a single standard paracentesis. However, all participants have resistant, recurrent ascites and are in need of repeated paracenteses weekly, bimonthly or monthly. Therefore, we consider the PleurX catheter to be a relatively proper and safe option for participants.

FINANCES AND INSURANCE

Insurance

Trial participants will be insured through the national patient insurance. Trial participants are informed of this relation in written information of trial participant’s rights, appendix 2. Sponsor and investigators are covered by their employment hospitals statutory insurance.

Finance and funding

PleurX catheters and drainage bottles will be purchased from Vingmed Danmark A/S. Drainage bottles for participants will be provided by Carefusion BD as a grant for device (up to 800 bottles). Carefusion BD does not provide financial support in addition to devices. Gastro Unit, medical division, Amager and Hvidovre Hospital will incur inpatient expenses during the trial.

Vingmed Danmark A/S is not further involved in the trial and has no influence whatsoever on the design and methodology, nor on compilation and publication of results.

Sponsor and initiator [name] has invented the overall template of this research project and has taken initiative to execute it. None of the involved investigators have economic or commercial conflicts regarding the investigations.

Investigators will be financed through clinical employments at their respective hospitals.

Expenses regarding trial investigations, admissions to hospital for the purpose of participating in the trial and extra outpatient visits will be undertaken by the involved hospitals.

Additional costs and expenses, including biochemical analyses and investigations will be covered through funds.

The trial has received grants from: University Hospital Hvidovre Research Foundation (2015; 84.000 Dkr.), Copenhagen University Internationalization Fund (2016; 120.000 Dkr.) and Hvidovre Hospitals Lægefond til bekæmpelse af Leversygdomme (2016; 30.000 Dkr).

PUBLICATION

The trial will be registered in clinical trial database www.clinicaltrials.gov before inclusion of the first patient. The results of the trial will be published in medical journals and conferences regardless of the results (positive, negative or inconclusive). We expect that the trial will lead to at least one publication. If we are unable to publish the result in a scientific journal, the results of the trial will be made public on www.clinicaltrials.gov.

LIST OF APPENDICES

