| **Visit 1** | **Day 0:**  Standard biochemical analysis, *Special biochemical analysis,*  assessment of ascetic fluid | | | | | | |  |
|  |  | | |  |  | | |  |
|  | PleurX 16 patients | | |  | Repeated paracentesis 16 patients | | |  |
|  |  | | |  |  | | |  |
| **Visit 2** | **Day 1:** Collect baseline data. Quality of life, Standard biochemical analysis*,* Nutritional parameters (weight, handgrip strength, BMI, *DXA scan),* | | | | | | |  |
|  |  |  |  | | |  |  |  |
| **Visit 3** | **1 month:** Assessment of ascetic fluid*, Quality of life, Standard biochemical analysis, Nutritional parameters (weight, handgrip strength, BMI) | | | | | | |  |
|  |  |  |  | | |  |  |  |
| **Visit 4** | **2 months:** Assessment of ascetic fluid*, Quality of life, Standard biochemical analysis, Nutritional parameters (weight, handgrip strength, BMI) | | | | | | |  |
|  |  |  |  | | |  |  |  |
| **Visit 5** | **3 months:** Assessment of ascetic fluid*, Quality of life, Standard biochemical analysis, Nutritional parameters (weight, handgrip strength, BMI, *DXA scan),* | | | | | | |  |
|  |  |  |  | | |  |  |  |
| **Visit 6** | **4 months:** Assessment of ascetic fluid*, Quality of life, Standard biochemical analysis, Nutritional parameters (weight, handgrip strength, BMI) | | | | | | |  |
|  |  |  |  | | |  |  |  |
| **Visit 7** | **5 months:** Assessment of ascetic fluid*, Quality of life, Standard biochemical analysis, Nutritional parameters (weight, handgrip strength, BMI) | | | | | | |  |
|  |  |  |  | | |  |  |  |
| **Visit 8** | **6 months:** Final assessment. Assessment of ascetic fluid*, Quality of life, Standard biochemical analysis, Nutritional parameters (weight, handgrip strength, BMI, *DXA scan), n* | | | | | | |  |

*Parameters written italic are assessed only at visit 1 or 2, 5 and 8.*

*Patients randomized to regular large volume paracentesis: Ascites fluid will be analyzed at each paracentesis. Patients randomized to PleurX catheter: Ascites fluid will be analyzed at visit 1 and visit 3-8.

Background

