Once the catheter is placed, drainage of ascites can be done using vacuum bottles connected to the catheter (see Appendix F). A home nurse will be trained in the drainage procedure and patient monitoring by specialised company staff from Vingmed. (http://www.carefusion.com/our-products/interventional-specialties/drainage/about-the-pleurx-drainage-system/patient-information-pleurx-system/how-to-drain-at-home). The home nurse will ensure that only a maximum of two litres of ascites fluid is removed at a time.

*Large volume paracentesis*: Removal of more than five litres of ascites is defined as large volume paracentesis. Initially, an abdominal ultrasound is performed. This allows an estimate of the ascites volume and distance from the skin to the ascitic fluid. The procedure is performed with the patient lying on his back in a slightly recumbent position toward the site of paracentesis. The ultrasound is used to ensure adequate insertion of the needle in the ascitic fluid. Generally, the insertion site is inferior to umbilicus 2-3 fingerbreadths below the umbilicus. The area is cleaned with betadine in and sterile drapes applied. Using sterile technique, local anesthesia is applied to the area from the skin to the peritoneum. A small incision is made (about 1.5 cm). Subsequently, the catheter, which contains a needle is inserted. Once fluid is aspirated, the needle is removed from the plastic catheter. The catheter is then attached to the catheter bag. After the procedure, the patient remains in hospital for observation until the fluid is drained. Vital signs are checked and the amount of fluid drained is registered. After removal of 4 liters, 25 cc of albumin (25% solution) is given for every following 3 liters of ascitic fluid removed.

Potential Risks

Risks associated with peritoneal catheter and large volume paracentesis

The risks associated with insertion of a peritoneal catheter and large volume paracentesis include pain at insertion of the drain, ascites leakage, haemorrhage, hypotention, electrolyte depletion, protein depletion, peritonitis, and bowel perforation. Based on previous evidence,^51 53^ the combined risk of these adverse events is 10% in both intervention groups.

*Pain*: Infiltration of the puncture site with a local analgesic will be used before insertion of the peritoneal catheter and large volume paracentesis. The administration of local anaesthetic may be pain free or be associated with a sharp sudden pain.

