We will screen potentially eligible patients admitted to the clinical sites based on daily generated lists of patients referred to in-hospital management or outpatient clinics. Patients with cirrhosis and diuretic resistant ascites will also be identified from records of patients followed in the outpatient clinics. Initial assessment of background information will be performed based on hospital records including demographics, primary diagnosis, co-morbidities, medical treatments, and surgical procedures. Patients who are potentially eligible will be approached by an investigator.

Patient history will then be re-evaluated to determine eligibility based on inclusion/exclusion criteria.

Potential participants will be provided with written and oral information as described below.

Visit 1 (Day 0)

- Patients have been fasting overnight.
- Ensure the informed consent
- Collection of:
- blood tests for standard biochemical analysis and special biochemical analysis (biobank)
- control of ascites (amount of ascites assessed using abdominal ultrasound)
- Conduct the allocated intervention procedure (PleurX insertion or large volume paracentesis)
- Patients allocated to PleurX are informed about the handling of the PleurX catheter including the importance of removing a maximum of two litres of ascitic fluid. The information will be repeated by the nurse at the home visit.
- Collect information about procedure related complications and adverse events.
- Ensure that the procedure is complete (ascitic fluid is mobilised using the PleurX catheter or large volume paracentesis).

Visit 2 (Day 1)

- Collection of information about:
- adverse events
- quality of life
- Collection of:
- blood tests for standard biochemical analysis
- weight and height
- hand grip strength
- Assessment of:
- Nutritional parameters (weight, handgrip strength, BMI, DXA scan)

Visit 3 (Day 30)

Outpatient visit including collection of information about control of ascites (amount of ascites assessed using abdominal ultrasound and number of paracenteses since the last visit), adverse events and quality of life.

Collection of blood tests for standard biochemical analysis, measurement of weight and hand grip strength and calculation of BMI.

Visit 4 (Day 60)

Outpatient visit including collection of information about control of ascites (amount of ascites assessed using abdominal ultrasound and number of paracenteses since the last visit), adverse events and quality of life.

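### Quality of life, grip strength, weight, BMI and DXA labelled as baseline are first taken on Day 1, after the allocated procedure, so any analysis that relies on them can be biased by treatment

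*Protocol*

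**What the plan says.** The flow chart places Visit 2 (Day 1) below the split into the two arms and gives it the task "Collect baseline data. Quality of life, Standard biochemical analysis", plus weight, grip strength, BMI and a DXA scan. The Trial Flow text agrees. Under Visit 2 it lists quality of life, standard bloods and "Nutritional parameters (weight, handgrip strength, BMI, DXA scan").

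The treatment comes one day earlier. Under Visit 1 (Day 0) the text says "Conduct the allocated intervention procedure (PleurX insertion or large volume paracentesis") and then "Ensure that the procedure is complete (ascitic fluid is mobilised using the PleurX catheter or large volume paracentesis"). The measurements listed for Day 0 are an ultrasound assessment of ascites and "blood tests for standard biochemical analysis and special biochemical analysis (biobank"). Quality of life, weight, grip strength and DXA are not among them.

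On volumes, the Interventions section states "Removal of more than five litres of ascites is defined as large volume paracentesis". For PleurX it states that the home nurse ensures "only a maximum of two litres of ascites fluid is removed at a time".

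Quality of life is a listed secondary outcome. The synopsis adds metabolic and biochemical changes, and the Rationale names nutrition as a possible benefit.

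**The concern.** A baseline value is useful because treatment cannot have influenced it. The Day 1 values do not meet that condition. The patient already knows the allocation, has had the procedure and has been drained. They are early post-treatment measurements under a baseline label.

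If such a value is subtracted from later values, or entered as a covariate, any treatment effect present on Day 1 is taken out of the later effect or added to it. At stake are quality of life and the nutritional measures. A statistical analysis plan could choose not to use Day 1, but it could not recover a pre-procedure value that the visit schedule never collects.

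**Working it through.** The protocol gives no figure to reproduce. The check is the order of events, followed by what that order does to an analysis.

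**1. Order of events (flow chart and Trial Flow text)**

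- Before Day 0: screening and consent.
- Day 0: bloods and ultrasound, then the allocated procedure, then confirmation that it is complete.
- Day 1: first quality-of-life questionnaire, weight, height, grip strength, BMI and DXA.
- Months 1 to 6: follow-up.

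The two sources match, so this is not a damaged table. Standard biochemistry is different: it is taken on both days, and its Day 0 sample is listed ahead of the procedure.

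**2. What can differ between arms by Day 1**

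- Knowledge of allocation: the Blinding section says neither patients nor investigators are blinded.
- Discomfort: Ethical Considerations says that placing the catheter is more uncomfortable than a single paracentesis.
- Volume drained: more than 5 L defines large volume paracentesis. The 2 L ceiling is written for home drainage and for instructing patients. The volume drained at catheter insertion is not given.

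**3. Effect on an analysis**

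Let D be the true difference between arms at a follow-up visit and d the difference that treatment has already produced on Day 1.

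- Follow-up comparison without Day 1: D.
- Change from Day 1: D − d.
- Adjustment for Day 1 with within-arm slope b: D − b × d.

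Illustrative values for change from Day 1:

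- d = 0: D − 0 = D, no bias.
- d = 0.25 D: D − 0.25 D = 0.75 D.
- d = 0.5 D: D − 0.5 D = 0.5 D.
- d of opposite sign, for example −0.25 D: D + 0.25 D = 1.25 D, an inflated effect.

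The protocol does not fix d, so any of these is possible.

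**4. Weight as an example (assumption: about 1 kg per litre)**

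Offset on Day 1 = litres removed by paracentesis − litres removed at PleurX insertion.

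- Paracentesis more than 5 L, PleurX 2 L: more than 5 − 2 = 3 kg.
- Paracentesis more than 5 L, PleurX 0 L: more than 5 − 0 = 5 kg.
- Both arms drained equally: about 0 kg.

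The unstated insertion volume decides where in this range the offset falls.

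**The case against.** The strongest reply is that the protocol specifies no analysis that Day 1 would bias. It lists quality of life as an outcome, not change in quality of life. Its statistical section names only general group comparisons for anything beyond the primary outcome. The word change is attached only to metabolic and biochemical parameters, and standard and special biochemistry have Day 0 samples. Comparing arms at months 1 to 6 without Day 1 is protected by randomisation. This stands: the bias is conditional, and a reader who infers that a planned change-from-baseline analysis is biased goes further than the text.

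Two other inferences are tempting and also fail.

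- That Day 1 weights must differ by at least 3 kg. This needs the 2 L ceiling to apply at insertion, which the protocol does not say. The Visit 1 completion check is worded alike for both arms and can be read as comparable drainage.
- That paracentesis patients would seem to deteriorate from a post-drainage peak while PleurX patients seem to recover from fresh incisions. Both arms have an incision of about 1.5 cm and both are drained on Day 0. The questionnaire and its recall period are not in the text at hand. Greater discomfort with placement is documented; the net direction on a score is not.

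It can also be said that weighing and scanning after drainage limits distortion by ascites. The protocol does not give this reason, but the choice is defensible for weight, BMI and DXA. It offers no defence for the questionnaire, nor an evident one for grip strength.

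Finally, the Adverse Events section says that the questionnaire is answered at every visit, which might seem to include Visit 1. Neither the flow chart nor the visit text lists it there.

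**Conclusion.** The point holds in a limited form. Quality of life, grip strength, weight, BMI and DXA have no scheduled value before treatment, and the Day 1 values should not carry a baseline label. An analysis using them as reference or covariate can be biased, by an amount and in a direction that the protocol does not determine. The 0 to more than 5 kg range for weight is an illustration that rests on 1 kg per litre and on an unstated insertion volume.

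Follow-up comparisons that leave out Day 1 remain valid, although they forgo baseline adjustment in a trial of 32 patients. Paracentesis-free survival is unaffected. For these reasons the correction is worthwhile for secondary outcomes but is not a must-fix.

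**What to change.** - Add the quality-of-life questionnaire, grip strength and a weight to Visit 1, after consent and before randomisation and the procedure. Use these as the baseline values. With height recorded, a baseline BMI follows from that weight.
- Keep post-drainage weight and DXA on Day 1 if wanted, but label them post-procedure and do not use them as a pre-treatment baseline. DXA would then be compared between arms at months 3 and 6 without baseline adjustment.
- Remove the baseline label from Visit 2 in the flow chart and align the visit text.

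The cost is an amendment to the visit schedule and a slightly longer Day 0 visit. No new type of assessment is needed. For patients already treated, the missing pre-procedure values cannot be recovered, so their follow-up values should be compared without Day 1.

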Repeated large volume paracentesis allows only temporary mobilisation of ascites and relief of symptoms. Insertion of a tunnelated peritoneal catheter (PleurX) allows repeated intermittent fluid drainage at smaller volumes. The PleurX catheter may therefore have beneficial effect on the management of ascites and improve quality-of-life as well as nutrition.

Objectives

To evaluate the beneficial and harmful effects of the PleurX catheter compared with large volume paracentesis.

Interventions

PleurX catheter compared with large volume paracentesis. Both interventions (PleurX catheter and large volume paracentesis) will be combined with albumin and the antibiotic ciproxin 500 mg once daily. The treatment with ciproxin 500 mg once daily will continue until the end of the trial. The PleurX cathether is approved for permanent placement. After completion of the trial, patients may choose to keep the PleurX or to have it removed.

*PleurX catheter*: The PleurX catheter is a tunnelated peritoneal catheter, designed for permanent placement in the peritoneal cavity (see appendix 6, pictures of the equipment). The catheter is placed by a trained, specialised physician under sterile conditions and with access to x-ray transillumination. All investigators involved in the placement of the PleurX catheter are specialised hepatologists with extensive experience in the management and observation of patients with refractory ascites including experience in the use of the PleurX and large volume paracentesis through their clinical work.

The catheter is 50 cm in length and is placed in the peritoneal cavity (Appendix). A small incision (approximately 1.5 cm) allows the catheter access to the peritoneal cavity from where fluid can be drained. The catheter is placed in a 5 to 8 cm subcutaneous tunnel and penetrates the skin at another incision. Initially, the catheter is attached to the skin with two sutures. A special cuff on the catheter allows entrenchment of the catheter in the subcutaneous fat. After 7-10 days, the incisions are healed and the catheter is simply wrapped in a soft bandage on the abdominal skin.

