- Diuretic resistant ascites defined as i) an inability to mobilise ascites (minimal or no weight loss) despite administration with the maximum tolerable doses of oral diuretics or a daily dose of spironolactone 400 mg and re-accumulation of fluid after therapeutic paracentesis within two weeks or ii) diuretic-related complications including (but not limited to) azotemia, hepatic encephalopathy, or progressive electrolyte imbalances;
- Able to read and understand Danish;
- Signed and dated informed consent form;
- Willing to comply with all study procedures and be available for the duration of the study;
- Male or female of any age;
- Age at least 18 years;
- Expected survival at least three months.

Patient Exclusion criteria

- Participants eligible TIPS, and planned for procedure within two months;
- Serum creatinine levels above 135 umol/L;
- Overt hepatic encephalopathy in the two weeks before randomization;
- Ascites due to other causes than cirrhosis such as: malignant disease, congestive heart failure, end-stage renal disease, pancreatitis, or Budd-Chiari (hepatic vein thrombosis), or chylous ascites;
- Ongoing intra-abdominal infection (peritonitis) or active systemic or local infections, such as urinary tract infection or pneumonia;
- Participation in a clinical study that may interfere with participation in this study;
- Evidence of extensive ascites loculation;
- Variceal bleeding within two weeks before randomisation;
- Intraabdominal surgery within four months before randomisation;
- Spontaneous bacterial peritonitis (neutrophil count>250/µl within 24 hours of randomization);
- Patients with an increased risk of procedure related complications as judged by the primary healthcare provider.

Strategies for Recruitment and Retention

Potentially eligible patients will be identified through daily assessments of patients treated at the clinical sites.

Sponsor and primary investigator will provide thorough information about the study design to specialised hepatologists at the recruiting sites. The trained physicians will then be authorized to identify eligible patients in their clinical practice. After conveying adequate study information to possible study participants the patients can either sign informed content or the physician can schedule an inclusion consultation with an investigator at primary site. If screened patients have no interest in taking part in the project we will register patient data in a screening log.

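### The second limb of the definition of diuretic resistant ascites does not require the recurrent need for paracentesis that the ethics section attributes to every participant

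*Protocol*

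**What the plan says.** Patient inclusion criteria opens the definition with "Diuretic resistant ascites defined as i) an inability to mobilise ascites (minimal or no weight loss" and continues to the point where the limbs meet: "re-accumulation of fluid after therapeutic paracentesis within two weeks or ii) diuretic-related complications". The return of fluid within two weeks thus belongs to limb (i). Limb (ii) reads "ii) diuretic-related complications including (but not limited to) azotemia, hepatic encephalopathy, or progressive electrolyte imbalances". The limbs are joined by an or.

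Two exclusions bear on the complications named in limb (ii): "Serum creatinine levels above 135 umol/L" and "Overt hepatic encephalopathy in the two weeks before randomization".

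Ethical considerations concedes that placing the catheter is more uncomfortable than one ordinary paracentesis. It answers that "all participants have resistant, recurrent ascites and are in need of repeated paracenteses weekly, bimonthly or monthly" and concludes: "Therefore, we consider the PleurX catheter to be a relatively proper and safe option for participants". The Rationale argues from the same premise: "Repeated large volume paracentesis allows only temporary mobilisation of ascites and relief of symptoms".

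The primary outcome is paracentesis free survival, and the cumulative number of paracenteses is a secondary outcome. Under Randomisation procedure, allocation is simple 1:1. Statistical analyses compares groups by t-test or chi-square test and the primary outcome by log-rank test.

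**The concern.** The trial compares a catheter with repeated paracentesis, so its question applies to patients whose ascites keeps returning. The protocol treats that as true of all participants and uses it in the benefit-risk argument, but the entry criteria do not secure it. A patient can satisfy limb (ii) through a diuretic-related complication, from a list left open, with no earlier paracentesis and no documented recurrence.

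Two things are at stake. The stated justification for the catheter may not apply to everyone who is randomised. And a patient without recurrent need contributes little to either paracentesis outcome: a control may need no further paracentesis after Day 0, and a catheter patient may hardly drain. With 32 patients, even a few would matter.

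**Working it through.** The protocol gives no figure for this point, so the first check is of the text and the second illustrates the consequence.

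**Text**

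| Condition | Limb (i) | Limb (ii) | Any other criterion | Ethical considerations |
|---|---|---|---|---|
| Ascites present | yes | yes, under the common heading | – | yes |
| Earlier therapeutic paracentesis | yes | no | no | implied |
| Fluid returns afterwards | yes, within two weeks | no | no | asserted for all |
| Need for repeated paracentesis | follows from recurrence | no | no | asserted for all |

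The creatinine and encephalopathy exclusions narrow two of the three complications named in limb (ii). Electrolyte imbalance and the open-ended part of the list remain. The gap is in the wording of limb (ii), and nothing else in the criteria closes it.

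**Size of the dilution (illustration only)**

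Let a fraction f of patients have no recurrent need and the same probability q of paracentesis free survival in both arms. An arm with probability p among the other patients then has

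p* = (1 − f)p + fq,

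and the difference between arms becomes (1 − f)(p₁ − p₂), whatever q is. The same factor applies to the mean paracentesis count if these patients have equal mean counts in the two arms.

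To express this as power, a comparator is needed. Sample Size Considerations gives one probability, 0.3, and no second one. I assume 0.8 because a two-sided 5% comparison of 0.3 with 0.8, without continuity correction, needs 15 per arm (power 79.1% at the stated 14). That is close to the plan's figure but does not reproduce it exactly. With 16 per arm,

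power = Φ{ [√n |d| − 1.96 √(2 p̄(1 − p̄))] / √[p₁(1 − p₁) + p₂(1 − p₂)] },

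where d is the difference and p̄ the mean of the two proportions. I take q from 0.5 to 1.0. The lower end corresponds to failure by death alone at the roughly six-month median survival given in the Background.

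| f (assumed) | Arms, q = 0.5 | Power | Arms, q = 1.0 | Power |
|---|---|---|---|---|
| 0 | 0.30 / 0.80 | 84.6% | 0.30 / 0.80 | 84.6% |
| 10% | 0.32 / 0.77 | 74.8% | 0.37 / 0.82 | 76.2% |
| 20% | 0.34 / 0.74 | 63.3% | 0.44 / 0.84 | 66.9% |
| 30% | 0.36 / 0.71 | 51.1% | 0.51 / 0.86 | 57.3% |

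This compares proportions at six months and stands in for the planned log-rank test. The values of f, q and 0.8 are assumptions.

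**Chance imbalance**

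If 6 of the 32 patients (19%, assumed) lacked recurrent need, simple randomisation would split them 5:1 or more unevenly with probability (1 + 6 + 6 + 1)/2⁶ = 14/64 = 22%. The same mechanism applies to the range of need, weekly to monthly, that the protocol itself describes.

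**Peritonitis figures**

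For the catheter in cirrhosis, the Background reports peritonitis after 19 of 200 placements, 9.5%. For paracentesis it reports 4 of 35 (11%) in one trial and 2 of 48 (4%) in a control group that combined diet, diuretics and paracentesis. Potential Risks puts the combined risk of the listed adverse events at 10% in both groups.

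**The case against.** The strongest reply is that a limb (ii) patient will in practice have recurrent ascites. Both limbs sit under the heading of diuretic resistance. The Background describes progression to resistance as mostly irreversible and says that the complications of diuretics often lead to their being stopped. It also says that diuretics are what keeps fluid from returning after paracentesis. At Visit 1 every patient has the allocated drainage procedure, and the control procedure is defined as drainage exceeding five litres, so a large volume is presupposed. Specialised hepatologists identify the patients, and two investigators check eligibility independently.

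Most of this stands. A reader might infer from limb (ii) that its patients have no need for repeated paracentesis and receive a permanent catheter from which they cannot benefit. The documents do not support that: the wording admits such a patient but does not imply one, the Background points the other way, and removal of the catheter is offered after the final visit.

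The reply does not remove the gap. Limb (ii) does not require that diuretics were stopped. Drainage on Day 0 shows fluid on one day, not recurrence. And the protocol writes recurrence as an explicit condition in limb (i), so it does not treat it as implied by resistance.

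A reader might also take 19 of 200 as an extra risk borne without benefit. That does not follow. The protocol's own figures for paracentesis are of similar size. The 200 are placements, with some patients counted more than once, in a study without a control group or data on antibiotics. Here both arms receive antibiotic prophylaxis.

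**Conclusion.** The point holds as an inconsistency between two sections. The eligibility criteria are broader than the premise on which Ethical considerations justifies the catheter, and the difference lies in limb (ii). This can be read off the page and needs no assumption.

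The statistical consequence is conditional. Any patient admitted without recurrent need would pull the arms together, by the factor (1 − f) on the difference. Under the assumed 0.3 against 0.8, a 10% share would lower power at 16 per arm from about 85% to about 75–76%. The protocol gives neither that share nor the comparator, so these figures show sensitivity and do not estimate a loss; the true share may be close to zero. No excess peritonitis risk over paracentesis is shown. The matter is worth correcting because it is cheap and the trial is small.

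**What to change.** Reconcile limb (ii) in Patient inclusion criteria with Ethical considerations, so that the criteria ensure the recurrent need which the latter asserts. The clinical wording is for the investigators to choose. Simply carrying the two-week window of limb (i) over to limb (ii) could exclude patients who need paracentesis monthly, whom Ethical considerations counts as participants, so the revision should be checked against that group.

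In addition, record from hospital records the number of paracenteses in a fixed period before randomisation, the same for every patient. Use it as a baseline covariate in the analysis of the cumulative number of paracenteses, in place of the unadjusted group comparison. Need ranges from weekly to monthly and simple randomisation of 32 patients does not balance it. The form of the model can be left to the SAP.

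The cost is one revised eligibility sentence, one CRF item from records already consulted at screening, and possibly a few limb (ii) patients without recurrence who would not be enrolled. If the statement in Ethical considerations is true of the intended population, and the wording keeps the monthly patients, no intended patient is lost.
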